## Abstract

**Background:**

Due to the lack of evidence to determine the best treatment for deep cavitated caries lesions in primary molars, the search for an effective restorative technique, which results in a minimal discomfort to patients, and reduce the time needed for the treatment, becomes relevant. The objective of this randomized clinical trial was to evaluate if high-viscosity glass ionomer cement (HVGIC) restorations is noninferior to restoration with calcium hydroxide cement associated with HVGIC for treatment of deep lesions in primary molars, as well as the impact of the treatments on cost and discomfort of the patient.

**Methods:**

A non-inferiority randomized clinical trial with two parallels arms (1:1) will be conducted. Children with 4 to 8 years will be selected at Clinic of Pediatric Dentistry at Ibirapuera University. 108 teeth will be randomized into two groups: (1) Calcium hydroxide cement associated with HVGIC and (2) HVGIC restoration. Primary outcome will be considered the pulp vitality and to be evaluated after 6, 12, 18 and 24 months by two calibrated examiners. Survival of restorations will also be evaluated in the equal intervals. The duration of dentals treatment and the cost of all materials used will be considered for estimating of cost-efficacy of each treatment. Individual discomfort will be measured after each dental procedure using the Wong-Baker’s Facial Scale. For the primary outcome, Kaplan-Meier survival and the long-rank test will be used to comparison between the groups. Cox regression will be performed to assess the influence of variables on the outcome. For all analyzes, the significance level is set at 5%.

**Discussion:**

Based on the philosophy of ART, our hypothesis is that the HVGIC restoration is a possible approach to restore the deep caries lesion with pulp vitality without the use of rubber dam and anesthesia.

**Trial registration:**

Clinicaltrials.gov registration NCT02903979. Registered on June 9th 2016.

**Electronic supplementary material:**

The online version of this article (10.1186/s12903-018-0703-3) contains supplementary material, which is available to authorized users.

## Background

In Pediatric Dentistry, a number of factors have contributed to the marked decline in dental caries rates [1, 2]. However, this is a disease that still deserves attention, given its involvement in all age groups and, mainly, its negative impact on children’s quality of life [3, 4].

With the better biological understanding of the disease, as well as the importance of the etiological and modifiers factors, new concepts were developed for treating of these lesions, especially those already cavitated, in order to use less invasive restorative techniques and preventive approaches [5]. These changes in the paradigms allow, therefore, the accomplishment of more conservative cavity preparations, with significant preservation of enamel and dentin, since it is possible only the removal of the irreversibly affected tissues by the caries lesion [6, 7].

The treatment of deep caries lesions closes to the pulp considered healthy, on the other hand, results in a challenge for the dentists [8], especially for a gap in well-designed studies that determine the best treatment for these lesions [9].

Considering the requirements of Minimal Intervention dentistry, indirect pulp capping has been described as an effective option for the treatment of these lesions [8]. Based on the technique of selective dentin caries removal, indirect pulp capping is performed in a single dental session and aims to use a biocompatible material to protect the dentin-pulp complex, such as calcium hydroxide cement [8], which would have as benefits the reduction of the number of remaining bacteria as well as a possible dentinal response leading to the formation of a reparative dentin [10]. Recent studies still have suggested the use of inert materials for this protection because they would also have the capacity to arrest the caries process [11] or, even, the direct restoration of the cavity with adhesive systems associated with resin composite [12] or resin-modified glass ionomer cement [13].

Nevertheless, the high viscosity glass ionomer cement (HVGIC), which has been the material of choice for medium and low deep cavities in Atraumatic Restorative Treatment (ART), has not been considered in the studies that focusing in treatment of deep caries lesion [14]. Using this material in pediatric dentistry seems to be an alternative to decrease the time required for the clinical care, due to the facility to perform the restorations with HVGIC. Considering the philosophy of ART, it will be possible to restore the deep caries lesion with pulp vitality without the use of rubber dam and anesthesia. However, to date, there are no well-designed clinical trials evaluating cost-efficacy as well as other important patient-centered outcomes of the treatment of deep caries lesions with HVGIC.

Thus, this study aims as primary outcome to compare the pulp vitality of two types of treatment for deep caries lesions in primary molars (HVGIC restoration and restoration with calcium hydroxide cement associated with HVGIC) by a non-inferiority randomized clinical trial with two parallel arms. The secondary outcomes will compare the survival of restorations, caries progression, cost-efficacy and discomfort between the two treatment options. Our hypothesis is that the dental pulp vitality of teeth restored with HVGIC do not differ from teeth restored with a pulp capping material.

## Methods/design

### Trial design and ethical considerations

A non-inferiority randomized, controlled, double blind (participant and examiner) clinical trial with two parallels arms (1:1) will be performed. The present protocol follows the guidelines of the Standard Protocol Items: Recommendations for Interventional Trials (SPIRIT) as detailed in online Additional file 1.

It was approved by the local ethics committee from the Faculty of Dentistry of the University Ibirapuera (registration no. 1.670.059) and was recorded in the database for registration of clinical studies (Clinicaltrials.gov registration NCT02903979).

### Sample size calculation and selection

Participants will be selected with ages ranging from 4 to 8 years searching for dental treatment, coming from the Clinic of Pediatric Dentistry of the Ibirapuera University, Sao Paulo, Brazil. The screening will be carried out under natural light with the aid of a wooden spatula. Children with potential for inclusion in the research will be referred for clinical examination. Children with at least one primary molar with deep cavitated caries lesion on the occlusal or occlusoproximal surfaces will be included.

Special needs patients using orthodontic appliance and / or systemic diseases that may influence the oral cavity, will be excluded. In addition, teeth with pulp exposure, spontaneous pain, mobility, abscess or fistula near the tooth, teeth with restorations, sealants or defects of enamel formation will be excluded.

Initial periapical radiography will also be performed to confirm the depth of the lesions as well as to exclude a possible pulpal involvement – presence of radiographically visible furca/periapical lesion - linked to clinical evaluation by PUFA index [15] - presence of ulceration, fistula and abscess, reported pain and pathological mobility. It will be considered as deep caries lesion those that will be located in the inner third of dentin.

To perform the sample size calculation, the expected success rates of pulp vitality using a calcium hydroxide cement as pulp capping material was considered 94% in 12–29 months [16]. It was considered that a clinically significant difference was 15% in the success rate between the groups. Therefore, considering a significance level of 0.05 and a power of 0.80, using a one-tailed test for non-inferiority studies, with a 20% increase due to a possible sample loss and 40% by cluster of more than one tooth per children, we reached the final rounded number of 54 teeth per group, resulting in 108 teeth in total [17].

Recruitment are taking place from November 2016 to April 2018. After allocation and treatment in one of the groups, with mean of 1 month per participant, these will be followed up for 24 months. Figure 1 displays the flow diagram of clinical trial’s phases.

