## Discussion

Studies focusing in smart and comfortable techniques to children’s treatment should be conducted in order to guide the dentists to use of friendly-patient approaches. Thus, this is the first clinical trial that will evaluate as primary outcome the success rate considering the pulp vitality between restoration with calcium hydroxide cement associated with HVGIC and HVGIC restoration for treatment of deep caries lesions in primary molars in according the philosophy of ART.

The evaluation of this outcome will take into account clinical signs associated with symptoms, since that the most of the previous studies considering the survival of restoration as the primary outcome and not pondering the pulp condition. However, the main reason to use the pulp capping material is to protect the pulp tissue. Thus, it should be considered in the evaluation.

Others secondary outcomes will be considered. The choice of outcome measures was based on the efficacy of the treatment, but also in patient-centered outcomes, thinking in about the practice-based evidence where the preference of patient should be englobed in the treatment choice. Analysis of cost will be also performed in order to project the incremental cost of the treatments with higher failure rate for the public health manager.

This is important to highlighted that it will not be possible the blinding of the operators because of the evident differences between the both techniques. Nevertheless, to minimize this situation, the allocation of the treatments will be only performer after the selective caries removal. Furthermore, the patient and examiner can be considered as blinded.

Thus, our study desires to answer if it is possible to restore deep caries lesion of primary teeth only with HVGIC considering the ART philosophy. Since that this hypothesis was sustained, the pediatric dentistry can be used a friendlier technique to deep caries lesion management.

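### Meeting the 15-point margin (21% against 6% pulp failure) cannot support a no-difference hypothesis or an unqualified conclusion for HVGIC alone

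*Protocol article*

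**What the plan says.** The sample-size section of the protocol article (Sample size calculation and selection) gives all the inputs:

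- Control rate: "the expected success rates of pulp vitality using a calcium hydroxide cement as pulp capping material was considered 94% in 12–29 months".
- Difference: "It was considered that a clinically significant difference was 15% in the success rate between the groups".
- Error rates: "considering a significance level of 0.05 and a power of 0.80", "using a one-tailed test for non-inferiority studies".
- Inflation: "with a 20% increase due to a possible sample loss and 40% by cluster of more than one tooth per children".
- Result: "we reached the final rounded number of 54 teeth per group, resulting in 108 teeth in total".

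The Background ends with the hypothesis: "Our hypothesis is that the dental pulp vitality of teeth restored with HVGIC do not differ from teeth restored with a pulp capping material". The Discussion states what follows from a positive trial: "Since that this hypothesis was sustained, the pediatric dentistry can be used a friendlier technique to deep caries lesion management".

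Both arms receive the same caries removal and the same HVGIC restoration. The control arm adds a calcium hydroxide liner (Treatment procedures). A primary-outcome failure is a major pulpal event such as visible pulp involvement, fistula, abscess or a furcal or periapical lesion. A repairable restoration defect does not count (Primary outcome).

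**The concern.** A non-inferiority result says only that a deficit as large as the margin has been ruled out. Here the expected control failure is 6%, so 15 points on the success scale is large relative to the event being prevented. The size is hard to see because the article states it against a 94% success rate and does not translate it into failures.

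The hypothesis and the closing conclusion ask for more than the margin can deliver: one speaks of no difference, the other of HVGIC alone becoming usable. A trial could meet its margin while the true pulp failure rate was materially higher without the liner, and the article's wording would still count the hypothesis as sustained. This point is about the size of the margin and the claim attached to it. It applies even if a confidence bound is correctly compared with 15 points.

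**Working it through.** **1. Reproduce the plan's figure.** Inputs from the sample-size section: success 0.94 in both arms, margin 0.15, one-sided alpha 0.05 (z = 1.645), power 0.80 (z = 0.842).

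n per arm = (1.645 + 0.842)² × 2 × 0.94 × 0.06 / 0.15² = 31.0

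31 × 1.2 = 37.2, rounded up to 38. Then 38 × 1.4 = 53.2, rounded up to 54, as stated. Without intermediate rounding the result is 52.1.

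Other readings do not fit. A relative 15% (14.1 points) gives 35.1, and 35.1 × 1.2 × 1.4 = 58.9. One-sided 0.025 gives 68 after inflation. A superiority comparison of 94% with 79% needs 64 per arm before inflation. The 15% therefore acts as an absolute non-inferiority margin with equal true rates, and the sizing arithmetic is sound.

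**2. Put the margin on the failure scale.** Expected control failure is 1 − 0.94 = 0.06. The ratio is 0.15 / 0.06 = 2.5. Failure at the margin is 0.06 + 0.15 = 0.21, and 0.21 / 0.06 = 3.5-fold.

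**3. Probability of declaring non-inferiority.** Binomial probabilities are summed over all pairs of failure counts, with control failure at 6% and one-sided 5%. Three tests are used: the Wald bound, the Newcombe bound and the Farrington-Manning score test. The last two agree to the digits shown, so each cell gives Newcombe/Farrington-Manning to Wald. Teeth are treated as independent at each n:

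- 32 is the base number before inflation (31.0 rounded up) and stands in for the effective size after loss and clustering.
- 45 is 54 / 1.2, after the planned loss.
- 54 is every randomised tooth.

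| True experimental failure | 32 per arm | 45 per arm | 54 per arm |
|---|---|---|---|
| 9% (1.5-fold) | 50–60% | 62–71% | 70–76% |
| 12% (2-fold) | 31–40% | 39–47% | 45–51% |
| 15% (2.5-fold) | 18–24% | 22–27% | 25–29% |
| 21% (at the margin) | 5–7% | 5–6% | 5–6% |

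**4. One outcome by hand.** With 54 per arm, 3 control and 6 experimental failures:

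- Difference: 6/54 − 3/54 = 0.0556.
- Standard error: √(0.1111 × 0.8889/54 + 0.0556 × 0.9444/54) = 0.0529.
- Wald upper bound: 0.0556 + 1.645 × 0.0529 = 0.143, below 0.15.

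An observed doubling passes by Wald. By the score test the most that passes against 3 control failures is 5.

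**5. Tighter readings of the same data.** With a 10-point margin at 45 per arm, a true doubling passes 16–20% of the time. If the true rates are equal at 94%, the power of each tighter step is:

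| Step | 32 per arm | 45 per arm |
|---|---|---|
| 10 points | 39–61% | 57–65% |
| 6 points | 22–34% | 28–40% |

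Sizing the trial on 10 points would need 70 per arm, or 118 after the same inflation (236 teeth in total). Sizing on 6 points would need 194, or 327 after inflation (654 in total).

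**The case against.** **A rationale may exist elsewhere.** The article condenses a fuller protocol, and the reasoning behind a margin is commonly left to that document. This stands, so a missing rationale is not part of the point.

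**A margin can buy something.** Shorter treatment, less discomfort and lower cost are trial aims and could justify accepting some loss of efficacy. This also stands, and it is a reason to keep 15 points for sizing. But a hypothesis of no difference leaves no room for such a trade.

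**The language may only be loose.** The Abstract states the objective as non-inferiority, the hypothesis follows a sentence naming a non-inferiority design, and the Discussion is conditional. That is fair, but the hypothesis as written is what the Discussion says would be sustained, and neither sentence carries the margin.

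**Stronger readings the article does not support.** A reader might infer that 15 points exceeds the whole benefit of the liner. The article gives no liner-versus-no-liner effect. The Background mentions inert materials and direct restoration as alternatives, but it also credits calcium hydroxide with reducing bacteria and promoting reparative dentin. A reader might also infer that any failure rate below 21% passes, or that a doubling would usually pass. Neither is so. The 21% is the hypothesis boundary, and a true 21% passes only about 5–7% of the time. A doubling is rejected more often than it passes in every case computed except Wald at 54 per arm, where it passes 51% of the time.

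**Conclusion.** The point holds as a mismatch between margin and claim. The margin is 15 percentage points, 2.5 times the expected control failure. Meeting it is compatible with a true failure rate well above control: a 1.5-fold rate passes about 50–76% of the time and a doubling about 31–51% (31–40% at 32 per arm). A positive result would show that an increase of 15 points or more has been excluded. It would not show that vitality does not differ, and it would not support an unqualified conclusion for HVGIC alone.

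The margin ratio and the 21% follow from the article's own figures. The pass probabilities also assume 6% true control failure, a one-sided 5% test and independent teeth, with 32 per arm standing in for clustering and loss. The sample-size calculation is not in error, and no claim is made about how large the liner's benefit is.

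**What to change.** Keep 15 points and 108 teeth, and make four changes:

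1. **Sample size calculation and selection:** state the margin as 15 percentage points, that is, 21% against 6% pulp failure.
2. **Background:** replace the no-difference hypothesis with non-inferiority within 15 percentage points. No non-inferiority margin, however tight, supports a statement of no difference.
3. **Data analysis:** report the one-sided 95% upper bound for the difference in 24-month failure. Read it in fixed sequence against 15, then 10, then 6 points (6 points being a doubling of the expected 6%). The margins are nested on one bound, so no alpha adjustment is needed.
4. **Discussion:** tie the conclusion to the step reached. If only 15 points is met, state that an increase of 15 points or more is excluded but smaller increases, including a doubling of the expected 6% failure, are not.

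The changes are to wording and pre-specification. They need no more teeth or visits, and the first test keeps its stated power. The cost is a more modest headline: as the power figures above show, the tighter steps may well not be reached even if the two treatments are truly equal.

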### Random allocation

The included teeth will be allocated in two parallels arms: Experimental group – HVGIC restoration, e Control group - restoration with calcium hydroxide cement associated with high viscosity glass ionomer cement (HVGIC). Teeth will be randomly assigned into one of groups considering the strata type of cavity – occlusal or occlusoproximal surfaces, according with the sequence obtained by an external researcher with a statistical software (MedCalc version 15.8, Ostend, Belgium). The randomization procedure will be performed per blocks of four. Table 1 displays the sample distribution in according experimental groups considering the strata.

**Table 1 Tab1:** Sample distribution in according experimental groups considering the strata

Groups Type of cavity	Experimental group	Control groups	Total
Occlusal	27	27	54
Occlusoproximal	27	27	54

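### The 40% cluster increase does not fit a trial that randomises single teeth; the error is conservative, and by the plan's own formula power is about 90%, not 80%

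*Protocol article*

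**What the plan says.** In Sample size calculation and selection, the protocol article gives these inputs:

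- Control success: "the expected success rates of pulp vitality using a calcium hydroxide cement as pulp capping material was considered 94% in 12–29 months".
- Difference to be excluded: "It was considered that a clinically significant difference was 15% in the success rate between the groups".
- Error rates: "considering a significance level of 0.05 and a power of 0.80, using a one-tailed test for non-inferiority studies".
- Increases: "with a 20% increase due to a possible sample loss and 40% by cluster of more than one tooth per children".
- Result: "we reached the final rounded number of 54 teeth per group, resulting in 108 teeth in total".

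Under Random allocation the unit is the tooth: "Teeth will be randomly assigned into one of groups considering the strata type of cavity", in blocks of four. The Abstract likewise speaks of 108 teeth being randomised. Under Allocation concealment mechanism, the envelope is opened at the restorative procedure, once caries removal is done. No section says that all teeth of one child go to the same arm. Under Data analysis, a Cox model with shared frailty is planned.

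**The concern.** Raising a sample by a factor of the form 1 + (m − 1) × ICC, with m teeth per child, is right when whole children are allocated to an arm, or when a single proportion is estimated from clustered teeth. In both cases correlated teeth add to the same mean. When teeth are allocated one by one, two teeth of one child are at least as likely to land in opposite arms as in the same arm. Their shared component then cancels in the arm difference at least as often as it accumulates. A 40% increase for clustering compensates for a loss of precision that the described design does not have.

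What is at stake is the description of the trial, not its validity. A reader judging a non-inferiority result would take 80% as the power of 54 teeth per group, but that figure describes a trial that allocates by child.

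**Working it through.** **Inputs.** From the protocol article: p = 0.94 for control, margin 0.15, one-sided alpha 0.05, power 0.80, 20% for loss, 40% for clustering, 54 teeth per group. Assumed: a true 94% in the experimental arm too, which is the usual non-inferiority default and the value that reproduces the plan's figure. The article gives neither an ICC nor the number of teeth per child, so values for these are assumptions.

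**Step 1: reproduce the 54.**

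n = (1.645 + 0.842)² × 2 × 0.94 × 0.06 / 0.15² = 31.0, so 31 per group.

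31 × 1.2 = 37.2, up to 38; 38 × 1.4 = 53.2, up to 54.

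Other orders of the two increases give nearly the same: 31 / 0.8 × 1.4 = 54.25, and 31 × 1.2 × 1.4 = 52.1. With the loss allowance alone the result is 37.2 or 38.75, so the stated total needs the 1.4.

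**Step 2: what tooth allocation does to the variance.** Code the arms +1 and −1. For children with m teeth each and correlation ρ, the design effect on the arm difference is

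DE = 1 + (m − 1) × ρ × E(a·a′),

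where a and a′ are the arm codes of two teeth of one child.

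| Allocation | E(a·a′) | DE for m = 2, ρ = 0.4 (illustrative) |
|---|---|---|
| By child | 1 | 1.40 |
| By tooth, independent | 0 | 1.00 |
| By tooth, both in one block of four | 1/3 − 2/3 = −1/3 | 1 − 0.4/3 = 0.87 |

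Simulation of 108 teeth with 1 to 4 per child, two strata and blocks of four agrees. With ICC 0.2 to 0.4 the design effect was 0.93 to 1.00 for tooth allocation and 1.17 to 1.60 for child allocation. Over ICC 0.1 to 0.5 the ranges were 0.88 to 1.00 and 1.13 to 2.01. These ranges are illustrative, but the formula shows that positive correlation cannot push the tooth-allocation value materially above 1.

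**Step 3: power by the plan's formula.** With k evaluable teeth per group,

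Power = Φ(0.15 / √(2 × 0.94 × 0.06 × DE / k) − 1.645).

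| Evaluable teeth per group | DE | Power |
|---|---|---|
| 54 × 0.8 = 43.2 | 1.4 | 0.798 |
| 43 | 1.0 | 0.900 |
| 43.2 | 1.0 | 0.902 |
| 54 / 1.2 = 45 | 1.0 | 0.912 |

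The first row shows that the 80% belongs to a design effect of 1.4. Without the factor, 80% power needs 38 (31 × 1.2, rounded up) to 39 (31 / 0.8, rounded up) teeth per group, or 76 to 78 in total instead of 108.

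**Step 4: how firm is the 90%?** Exact binomial power for independent teeth, 15-point margin, one-sided 5%, 94% in the control arm:

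| Teeth per group | True experimental success | Unpooled Wald | Farrington-Manning score |
|---|---|---|---|
| 31 | 94% | 82% | 73% |
| 43 | 94% | 89% | 82% |
| 45 | 94% | 91% | 85% |
| 43 | 92% | 76% | 67% |

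Only about 43 × 0.06 = 2.6 failures are expected per group, so the choice of test matters.

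**The case against.** Four objections deserve an answer.

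**The 0.80 is a target, not a claim about 108 teeth.** It enters the calculation as an input, and reserves added on top keep power at or above it. This is fair, and it is why the point is minor. But the 40% is not presented as a reserve: it is attributed to clustering, and with that attribution the sentence ties 54 teeth per group to 80%.

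**The article may not exclude that a child's teeth share an arm.** The recruitment paragraph speaks of allocation and treatment per participant, discomfort and visits are recorded per child or patient, and the flow diagram is not shown. If a child's teeth do share an arm, 1.4 is the right kind of factor. The Abstract and Random allocation nevertheless both name teeth as the unit, and the strata are a property of the tooth. The loose wording does not override them, but it is reason to ask for an explicit statement before the factor is removed.

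**About 90% is fragile.** This stands. It belongs to the normal approximation or a Wald test with equal true success of 94%. With a score test the sample sits only a few points above 80%.

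**A reader might infer more than the documents support.** One inference is that the trial is mis-sized in a harmful way. It is not: the error adds teeth, does not bias the estimate and does not raise the type I error. Another is that the sample can simply be advertised as having 90% power, or 80% power for a difference smaller than 15 points. Step 4 shows that either would be optimistic unless the test and the assumed success rates are named. A third is that clustering may be ignored altogether. Tooth allocation removes the inflation from the planning variance, not the correlation from the data, so the planned shared-frailty model is not made redundant.

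**Conclusion.** The point holds as a minor one. The stated 54 per group includes a 1.4 factor for clustering that does not match tooth-level randomisation, under which the design effect on the arm difference is about 1 or slightly below. By the plan's own formula, with 94% in both arms, a 15-point margin, one-sided 5% and 43 to 45 evaluable teeth per group, power is about 90%, some 10 to 11 points above the stated 80%. Under a Farrington-Manning score test it is about 82 to 85%, and it is lower under any test if true success with HVGIC alone is below 94%. The direction is conservative and no conclusion of the trial is threatened. All of this rests on the teeth of one child being randomised independently, as the Abstract and Random allocation describe.

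**What to change.** Keep 108 teeth. State explicitly that teeth of one child are randomised independently and may fall in different arms. Then choose one of two wordings:

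- Remove the 40% as a clustering adjustment and restate the power with its formula, test and assumptions: about 90% by the plan's formula or a Wald test, about 82 to 85% by a Farrington-Manning score test, at 43 to 45 evaluable teeth per group with 94% success in both arms. Note that it falls if true success with HVGIC alone is lower.
- Keep the 40%, but call it a safety reserve and not a design effect.

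If a child's teeth are in fact kept in one arm, correct the randomisation text instead, and give the ICC and the number of teeth per child behind the 1.4.

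In either case keep within-child clustering in the analysis model. The cost is one or two corrected sentences. If teeth are randomised as described, recruitment, allocation and data collection do not change.
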